### Intervention and control groups

Pregnant women will be randomly assigned into one of four groups. The control group will receive only routine care (newborn eye care, vitamin K_1_, immunizations, weighing, and examinations) after birth, whereas the intervention group will receive EENC including delayed cord clamping, immediate and sustained SSC, initiating exclusive breastfeeding, and routine care. The flow chart of EENC for cesarean section is showed in Fig. 2. Delayed cord clamping is defined as cutting umbilical cord until cord pulsations have ceased (approximately 1–3 min after birth) [18]. Immediate and sustained SSC is regarded as placing of the naked baby prone on the mother’s bare chest immediately after birth without separation [10]. Pairs of mothers and newborns in the intervention group 1, intervention group 2, and intervention group 3 will perform SSC for 30 min, 60 min, and 90 min, respectively.

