### Sample size calculation

We calculated the sample size based on the rate of early initiation of breastfeeding, which is one of the primary outcomes in this study. According to our pilot investigation and previous literature [4, 20], the rate of early initiation of breastfeeding is 40% in the control group (receiving routine care), and the rates in the intervention group 1 (receiving EENC with SSC for 30 min), intervention group 2 (receiving EENC with SSC for 60 min), and intervention group 3 (receiving EENC with SSC for 90 min) are supposed to be 60%, 70%, and 80%, respectively. Accounting for multiple comparisons (SSC for 30 min vs. routine care, SSC for 60 min vs. routine care, SSC for 90 min vs. routine care, SSC for 30 min vs. SSC for 60 min, SSC for 30 min vs. SSC for 90 min, SSC for 60 min vs. SSC for 90 min), a level of significance is set to be 0.008 (0.05/6) by using Bonferroni adjustments. For 80% power, the sample size required for each of the control group and the intervention group 1 is 152 participants; the sample size required for each of the control group and the intervention group 2 is 64 participants; the sample size required for each of the control group and the intervention group 3 is 34 participants. The largest sample size group (*n*=152) is selected as the number of recruitment in each group. Considering 15% of loss to follow-up, the number of participants in each group is finally set to be 180 and adds up to a total of 720 participants. One hundred eighty participants will need to be recruited in each of four hospitals, which means that each of the hospital will recruit 45 participants in the control group, intervention group 1, intervention group 2, and intervention group 3, respectively. The sample size calculation was performed using PASS 2011 software (NCSS, Kaysville, UT, USA).

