### Analysis plan

Baseline characteristics of participants will be presented as mean (standard deviation) for continuous variables and number (percentage) for categorical variables. Data will be analyzed on an intention-to-treat basis to compare primary and secondary outcomes in four groups. The chi-square test or one-way analysis of variance will be used to compare the characteristics and rates of exclusive breastfeeding and early initiation of breastfeeding, and maternal and neonatal outcomes among the 4 groups (control group, intervention group 1, intervention group 2, and intervention group 3). For missing data, we will use multiple imputation to obtain complete datasets. All the statistical analyses will be conducted using SPSS 20.0 statistical software (SPSS Inc., Chicago, Illinois). A two-sided *P* value <0.05 indicated significance.

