## Discussion

In China, EENC during vaginal deliveries has been performing since 2016 and contributed to increased rates of exclusive breastfeeding and improved maternal and neonatal health [4, 6, 15], while the evidence during cesarean deliveries remains lacking. The objective of this multi-centered randomized controlled study is to evaluate the effectiveness of EENC for cesarean section newborns on exclusive breastfeeding rates and early initiation of breastfeeding rates in China.

To the best of our knowledge, this study is the first multi-centered randomized controlled trial with relatively large sample size to determine the impact of EENC on improvement of breastfeeding outcomes and maternal and neonatal health for cesarean section newborns in China. We will recruit eligible women from four tertiary hospitals in four provinces that have been providing EENC during vaginal deliveries and accumulated abundant experience in EENC practices. All obstetricians, midwives, and researchers involved in implementation of EENC in four study sites were coached by national facilitators and passed post-coaching evaluations. Another strength of this study is that we will examine associations between the duration of SSC and breastfeeding performance, which will provide evidence-based recommendation to inform optimal duration of SSC for cesarean deliveries. The results of this study have potential to inform national-level guidelines and policy-making for optimizing EENC implementation for cesarean section newborns.

There are several limitations in this study. First, we currently focus on healthy mother and newborn pairs. Further studies will be needed among low-risk and high-risk mothers and newborns. Second, all study sites are tertiary-level hospitals with specialized obstetricians and midwives and advanced medical devices to ensure safety of mothers and newborns. In future studies, we plan to extend EENC implementation for cesarean section newborns to all levels of hospitals.

In conclusion, this is the first multi-centered randomized controlled study in China to assess the impact of EENC on improvement of breastfeeding outcomes and explore the optimal duration of SSC among newborns born by cesarean section. Our findings will enable making evidence-informed guidelines and policies.

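### The only outcome test in the Analysis plan is a four-group comparison that includes the no-EENC control, so its P value cannot answer the trial's stated question about skin-to-skin duration

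*Protocol article*

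**What the plan says.** **Aim.** The Discussion counts this as a strength: "we will examine associations between the duration of SSC and breastfeeding performance, which will provide evidence-based recommendation to inform optimal duration of SSC". The Discussion paragraph of the Abstract promises the same recommendation.

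**Test.** The Analysis plan names one outcome comparison, a chi-square test or one-way ANOVA "among the 4 groups (control group, intervention group 1, intervention group 2, and intervention group 3"). The level is given as "A two-sided *P* value <0.05 indicated significance". It mentions no contrast between EENC arms and no test that uses the ordering of 30, 60 and 90 min.

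**Arms.** Under Intervention and control groups, control receives routine care only, whereas "the intervention group will receive EENC including delayed cord clamping, immediate and sustained SSC, initiating exclusive breastfeeding, and routine care". The three EENC arms differ from each other only in planned SSC minutes.

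**Sample size.** This section lists six pairwise comparisons, three of them between EENC durations (30 v 60, 30 v 90 and 60 v 90 min), and says "a level of significance is set to be 0.008 (0.05/6) by using Bonferroni adjustments". It assumes that "the rate of early initiation of breastfeeding is 40% in the control group (receiving routine care") and that the 30, 60 and 90 min rates "are supposed to be 60%, 70%, and 80%, respectively". These are rates of early initiation of breastfeeding. The article gives no rates by arm for exclusive breastfeeding at discharge.

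**The concern.** The duration question has a specific null: among pairs who receive EENC, the outcome does not depend on SSC minutes. The null of the stated test is that all four groups, control included, have the same rate. Control is not a zero-minute level of the same treatment, because it also lacks two other components of the package. Any benefit shared by the three EENC arms makes the four-group null false even if 30, 60 and 90 min are equivalent. A trend test run over all four groups would have the same weakness, so ordering the arms does not help while control is included.

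At stake is the question that sets this trial apart. If EENC works about as well as assumed, the one stated P value will almost certainly be significant whatever the truth about duration. A recommendation on duration would then need support from some other analysis, and the Analysis plan does not name one.

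**Working it through.** **Inputs (Sample size calculation).** Control 40%; EENC arms 60%, 70%, 80%; 152 evaluable and 180 randomised per arm; alpha 0.008 (0.05/6); power 80%. From the Analysis plan: alpha 0.05, two-sided.

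**1. The plan's own sample size.** Two proportions, pooled variance under the null:

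n = [z(α/2)·√(2·p̄·q̄) + z(β)·√(p₁q₁ + p₂q₂)]² / (p₂ − p₁)²

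For 40% v 60% at 0.008: (2.652 × 0.7071 + 0.8416 × 0.6928)² / 0.04 = 2.458² / 0.04 = 151.1, so 152, as stated. The same formula gives 66 and 36 for the other two control comparisons (stated 64 and 34), a difference of no consequence here. 152 / 0.85 = 178.8, so 179, against 180 stated. Required sizes are given only for the three comparisons with control.

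**2. The four-group test when duration has no effect.** With equal arms of size n, the chi-square test with 3 df has noncentrality λ = n·Σ(pᵢ − p̄)² / [p̄(1 − p̄)] and critical value 7.815 at 0.05.

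For 40/60/60/60%: p̄ = 0.55; Σ = 0.0225 + 3 × 0.0025 = 0.03; 0.03 / 0.2475 = 0.1212; λ = 152 × 0.1212 = 18.4.

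| Common EENC rate (control 40%) | Significant, n=152 | Significant, n=180 |
|---|---|---|
| 50% (assumed) | 41% | 47% |
| 55% (assumed) | 77% | 85% |
| 60% | 96.3% | 98.4% |
| 70% | >99.9% | >99.9% |
| 80% | >99.9% | >99.9% |

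Simulation with 200,000 runs per case agrees to within 0.4 percentage points. At 0.05/6 instead of 0.05, the 60% row becomes 87% and 93%.

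**3. Tests restricted to the three EENC arms when duration has no effect.** At 0.05, for common rates of 60% to 80% and n of 152 or 180, a linear trend in minutes rejects 4.8% to 5.3% of the time and a 2-df chi-square 5.0% to 5.1%.

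**4. The three EENC pairs in the Sample size calculation.** When duration has no effect, the chance of at least one significant pair is about 2.2% to 2.3% at 0.05/6 and about 12% to 13% at unadjusted 0.05. Power under 60/70/80% at 0.05/6:

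| Pair | n=152 | n=180 |
|---|---|---|
| 30 v 60 min (60% v 70%) | 21% | 26% |
| 60 v 90 min (70% v 80%) | 26% | 33% |
| 30 v 90 min (60% v 80%) | 88% | 94% |

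Example, 60% v 70% at n=152: [0.10 − 2.638 × √(2 × 0.65 × 0.35 / 152)] / √((0.24 + 0.21) / 152) = (0.10 − 0.1443) / 0.0544 = −0.81, so 21%.

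**5. Linear trend within the EENC arms against 30 v 90 min.** With three equal arms equally spaced in minutes, the trend weights are −1, 0, +1, so the trend statistic also rests on the 90 minus 30 min difference. Under 60/70/80% at n=152 and 0.05: (0.20 − 1.96 × √(2 × 0.70 × 0.30 / 152)) / √((0.24 + 0.16) / 152) = (0.20 − 0.1030) / 0.0513 = 1.89, so 97%. At n=153 both tests have 97% power at 0.05 and 89% at 0.05/6. Under a smaller gradient (assumed 60/65/70%) both have 45% at 0.05 and 21% at 0.05/6.

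**The case against.** The strongest reply is that duration is not left to the four-group test alone. The Sample size calculation names all three comparisons between EENC durations and gives them a Bonferroni level. Those pairs exclude control, have the right null and keep false duration findings low. This stands, and a reader who inferred that the article contains no valid duration comparison would be wrong. What remains is that the pairs appear only as the reason for the sample-size alpha. The section that governs the analysis omits them and states 0.05 instead of 0.008. The trial is sized only for comparisons with control, so the adjacent steps, which bear most directly on an optimum, are weakly powered under the plan's own rates.

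A reader might also take 96% to 100% as a false-positive rate. It is not one: in those scenarios the four rates differ, and the chi-square test is right to reject. The figure would describe an error only if a significant overall P were read as a duration effect, and the article does not say that it will be. It also depends on EENC rates of 60% or more.

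A third tempting claim is that a trend test would be more powerful than the listed pairs. At equal alpha it is essentially the 30 v 90 min comparison, so no such gain exists.

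Finally, this is a condensed article and a fuller plan may specify more. The absence of a trend model would not be a finding by itself. The finding is that the stated test does not match the stated aim and that two sections of the article disagree.

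**Conclusion.** The concern holds in a limited form. The test stated in the Analysis plan cannot distinguish a duration effect from a package effect. With no duration effect it is significant 96% to 100% of the time at common EENC rates of 60% to 80%, and 41% to 47% of the time at 50%. The duration pairs and the 0.008 level in the Sample size calculation are not carried into the Analysis plan, and the two adjacent pairs have 21% and 26% power at 152 per arm.

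These figures assume a 40% control rate, equal arms of 152 to 180, independent binary outcomes and no adjustment for hospital. They use early-initiation rates. Power for exclusive breastfeeding at discharge cannot be computed from the article. The point does not show that the design is unable to address duration: the randomised arms support a valid comparison, and 30 v 90 min is well powered if the assumed rates hold. It is a correction worth making before analysis, not a fatal flaw.

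**What to change.** In the Analysis plan:

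- Keep the four-group test as a global test only, and say that it does not address duration.
- Reconcile this section with the Sample size calculation: state whether the six pairs will be tested, and at which level.
- Pre-specify one duration analysis in the three EENC arms, without control: logistic regression with SSC minutes (30, 60, 90) as a linear term and hospital as a factor, since randomization is stratified by site. Report the effect per 30 min with its 95% CI, together with the three arm estimates. Give it a stated place and alpha in the testing order.
- Include exclusive breastfeeding at discharge as an outcome for this analysis. Early initiation is settled within one hour of birth, before 90 min of SSC ends, so the 60 and 90 min arms have the same planned SSC throughout that window.
- Base statements about duration on the slope and arm estimates, not on the four-group P value.

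The cost is wording and one more model on data already collected, with no extra participants or procedures. There are two drawbacks. One more test needs a place in the testing order. A linear slope alone cannot locate a plateau, which is why the arm estimates should accompany it. The case for the model is that it asks the right question and gives an estimate with an interval; it should not be presented as more powerful than 30 v 90 min.

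### The trial is sized for six pairwise tests at 0.008, but the analysis plan names only a four-group test judged at P<0.05

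*Protocol article*

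**What the plan says.** The two relevant sections of the protocol article read as follows.

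- **Sample size calculation.** The section begins "Accounting for multiple comparisons (SSC for 30 min vs. routine care, SSC for 60 min vs. routine care" and goes on to list all six pairs: three EENC arms against control and three comparisons between durations. It then states: "a level of significance is set to be 0.008 (0.05/6) by using Bonferroni adjustments". The arm size follows from that level: "For 80% power, the sample size required for each of the control group and the intervention group 1 is 152 participants". This is raised to 180 per arm for 15% loss to follow-up.
- **Analysis plan.** The only tests named are these: "The chi-square test or one-way analysis of variance will be used to compare the characteristics and rates of exclusive breastfeeding and early initiation". The comparison is made "among the 4 groups (control group, intervention group 1, intervention group 2, and intervention group 3". The section ends with a two-sided P "value <0.05 indicated significance". It mentions no pairwise test, does not carry over 0.008, and exempts no outcome from the 0.05 rule.

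The Discussion sections of the abstract and of the main text promise evidence on the optimal duration of skin-to-skin contact, with possible use in national guidelines.

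**The concern.** The trial asks whether EENC is better than routine care and which duration of skin-to-skin contact is best. Both are questions about specific pairs of arms. A four-group test has three degrees of freedom, and its rejection says only that the four rates are not all equal. Someone must then compare pairs, and the only threshold the Analysis plan offers is 0.05.

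That threshold drops the Bonferroni protection for which the trial was enlarged. The likely casualty is a false claim that one duration beats another, which is the claim most likely to shape a recommendation. The trial is also open-label. With two thresholds on paper, the choice between 0.008 and 0.05 could be made after the results are known.

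**Working it through.** **1. Does the sample size depend on 0.008?**

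Inputs from the Sample size calculation: 40% in control; 60%, 70% and 80% in the 30-, 60- and 90-minute arms; 80% power. The test is taken as two-sided, as in the Analysis plan. The pooled-variance formula per arm is

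n = [z(1−α/2)·√(2p̄(1−p̄)) + z(0.80)·√(p₁(1−p₁)+p₂(1−p₂))]² / (p₁−p₂)²

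Control against 30 minutes (p̄ = 0.5, difference 0.2):

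- α = 0.008: (2.652×0.7071 + 0.8416×0.6928)² / 0.04 = 2.4584² / 0.04 = 151.1, so **152**, the stated figure.
- α = 0.05: (1.960×0.7071 + 0.8416×0.6928)² / 0.04 = 1.9690² / 0.04 = 96.9, so **97**.

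The other two comparisons with control give 66 and 36 at 0.008, close to the stated 64 and 34. The arm size therefore rests on the adjusted pairwise level. It is 152/97 = 1.57 times what 0.05 would need.

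**2. What does the four-group test deliver?**

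Under the planned rates of 40/60/70/80%, its power at 0.05 is above 99.9% at 152 per arm. Rejection is almost certain but identifies no pair.

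**3. What happens if pairs are read at 0.05?**

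The six pairs share arms and are correlated, so the error rates were simulated: 400,000 trials per scenario, pooled z-tests.

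*All four arms equal: probability of at least one significant pair among six*

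| Per arm | Common rate | Pairs at 0.05, no gate | Pairs at 0.008, no gate | Pairs at 0.05 after a significant four-group test |
|---|---|---|---|---|
| 152 | 40% | 21.3% | 4.1% | 5.0% |
| 152 | 50% | 18.6% | 3.6% | 5.0% |
| 180 | 40% | 19.6% | 4.1% | 5.0% |

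For reference, six independent tests at 0.05 would give 1 − 0.95⁶ = 26.5%. The Bonferroni bound at 0.008 is 6×0.008 = 4.8%.

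*EENC works but duration does not matter: probability of a false difference between durations, among three pairs, after a significant four-group test*

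| Per arm | True rates | Four-group test rejects | Pairs at 0.05 | Pairs at 0.008 |
|---|---|---|---|---|
| 152 | 40/60/60/60% | 96% | 12.8% | 2.3% |
| 180 | 40/60/60/60% | 98.5% | 11.8% | 2.3% |
| 152 | 40/70/70/70% | >99.9% | 12.4% | 2.2% |

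The equal-duration patterns are assumptions, chosen because they are the cases in which a duration claim would be false.

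**The case against.** The strongest reply is that the sections can be reconciled. The 0.05 could be the overall level, with a four-group test first and Bonferroni pairs at 0.008 after it, or with adjusted P values compared with 0.05. The pairs and their level are written down in the sample size section, and an article may leave the follow-up procedure to a statistical analysis plan. The 21% describes six ungated tests, which the protocol nowhere prescribes; with the four-group test as a gate, the error when all arms are equal is 5.0%.

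Part of this stands. The 21% is an ungated figure and moves with the assumed common rate, from about 19% to 21% in the table. Six comparisons set the level, but n was calculated only for the three against control.

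The rest does not rescue the plan. Neither reconciling procedure is stated, and the article gives two different levels rather than staying silent on one. The gate protects only the case in which all four arms are equal. Once EENC beats control the gate is nearly always open, and the false-duration rate at 0.05 stays at about 12% to 13%.

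**Conclusion.** The concern holds. The sample size section and the Analysis plan conflict on the test and on the significance level for the primary outcomes, and the stated 152 per arm reproduces with the 0.008 pairwise test.

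- Followed literally, the Analysis plan cannot say which duration works.
- With six ungated pairs at 0.05, family-wise error is about 19% to 21% when all arms are equal (common rate 40% or 50%), against about 4% at 0.008.
- With the four-group test as a gate, false claims between durations run at about 12% to 13%, against about 2%, when the EENC arms are truly equal at 60% or 70% and control is 40%.

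These figures apply to one primary outcome and assume pooled z-tests with 152 or 180 per arm. They show what happens if pairs are read at the Analysis plan's 0.05. A team that applied 0.008 would avoid the inflation, but the Analysis plan does not tell it to.

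**What to change.** In the Analysis plan:

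1. Name the six pairwise contrasts as the confirmatory tests for the primary outcomes, each judged two-sided at 0.05/6 = 0.0083, or by Holm over the same six. Report risk differences with intervals at the matching level: 1 − 0.05/6, or 99.17%, under Bonferroni.
2. Treat the four-group test as descriptive, and limit P<0.05 to secondary and descriptive analyses.

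A fully stated closed or gatekept procedure would also do, provided it protects the comparisons between durations and not only the case where all arms are equal.

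The cost is two sentences, with no added participants or data. A pairwise P between 0.0083 and 0.05 could no longer be called significant under Bonferroni, which is the bar the sample size already assumed.

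Two related limits should be acknowledged in the same edit:

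- At 0.008 and 152 (180) per arm, power under the planned rates is 88% (94%) for 30 against 90 minutes. It is only 20% (25%) for 30 against 60 and 26% (32%) for 60 against 90, so a non-significant result between adjacent durations should not be read as equivalence.
- The 0.05/6 covers one primary outcome. The protocol has two and should say whether either alone can declare success. If so, the family is twelve tests, not six.

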## Data management and monitoring

The data will be stored on h6world platform (h6world.cn). The research team will be given password to access this platform and obtain the data for analysis and interpretation. The data are monitored and audited annually by the Biomedical Research Ethics Committee of Peking University First Hospital. The data monitoring committee is independent from the sponsor and has no competing interests, and it will ensure that data management will be conducted according to the study protocol.

To ensure the confidentiality of the study data, each study participant will receive a unique identification number that will not be created by using their identifiable information. Only the research team will have access to the study data, and the data will not be shared with others.

## Plans for communicating important protocol modifications to relevant parties

Amendments to the study protocol will be communicated to the Biomedical Research Ethics Committee of Peking University First Hospital, and the research team. Participants to be recruited will be given a modified version of the study protocol before informed consent.

